#### Visceral adipose tissue and regional adipose tissue pools

3T MRI (Siemens Prisma at both sites) will be used to quantify all AT volumes including the primary outcome of visceral AT. We will use standard chemical shift-encoding MRI and custom PROFIT1^(30)^ pulse sequences for image acquisition without contrast agents. Abdominal AT (both visceral and subcutaneous) and liver AT fraction will be captured from three axial slices prescribed at the centre of the third lumbar vertebra and the middle of liver, respectively. Thigh muscle and AT will be acquired from ten axial slices of both thighs starting 10 cm from the most distal portion of the femurs.

#### Metabolic syndrome severity

Metabolic syndrome will be classified according to the National Cholesterol Education Program Adult Treatment Panel III panel definition, and the severity z-score will be calculated through sex- and ethnic-specific equations^(31)^. The required blood samples will be collected by venipuncture following an overnight fast. Waist circumference and blood pressure will be measured by the study team using standardised procedures.

#### Cardiovascular risk estimate

The Framingham 10-year CVD risk score will be calculated using the Canadian Cardiovascular Society sex-specific scoring system incorporating points for age, total cholesterol, HDL, treated/untreated systolic blood pressure, diabetes, and smoking status. The Reynolds risk score will be calculated using the same variables as well as family history of heart attack (self-report) and C-reactive protein.

#### Cardiopulmonary exercise test and resting metabolic rate

We will measure cardiorespiratory fitness by the gold standard cardiorespiratory fitness assessment, an incremental-to-maximum exercise test with open-circuit indirect calorimetry. Monitoring before, during and after the test will include heart rate, pulse oximetry, blood pressure and the Borg rating of perceived exertion. Prior to the exercise test, resting metabolic rate will be assessed by using the same metabolic cart during 10–30 min of supine fasted rest.

#### Circulating biomarkers

Participants will be asked to complete an overnight water-only fast prior to venipuncture. Core laboratories at each site will analyse fasting insulin, glucose, lipid profile, hemoglobin A1c and C-reactive protein in fresh blood, while blood will be stored (in each location) at −80°C for later batch analysis of leptin, adiponectin, IL-6, and TNF-*α*, and potentially other related markers of cardiometabolic health that may help to uncover mechanisms.

#### Physical activity and sleep

A Fitbit wrist-worn tracker with heart rate monitoring will be used to collect data on average time spent performing physical activity of various intensity levels, sleep duration and quality data, and resting heart rate.

#### Dietary intake

Dietary intake will be assessed by 3-d diet records over two consecutive weekdays and one weekend day. Each of three 24-h records will be collected using the Canadian version of the Automated Self-Administered 24-h Dietary Assessment Tool (ASA24-Canada)^(32)^. Calorie, macronutrient and micronutrient intake will be analysed.

#### Questionnaires

Chemotherapy symptom presence and severity will be assessed by the Rotterdam Symptom Checklist, which has been validated in patients with cancer^(33)^. The RAND-36 Health Survey and the European Organisation for Research and Treatment of Cancer Quality of Life Questionnaire will be used to evaluate health-related quality of life. Menopausal symptom presence and severity will be assessed by the Menopause-specific Quality of Life questionnaire^(34)^. Fatigue will be assessed by the multidimensional fatigue inventory which is validated within cancer populations^(35)^. Presence and severity of depressive symptoms will be assessed using the Patient Health Questionnaire-9^(36)^. Psychosocial stress will be evaluated by the reliable and validated perceived stress scale^(37)^. Demographics, alcohol intake, smoking status and CVD risk factors will be collected by questionnaire. At the end of the intervention period in the intervention group only, acceptability of each component of the intervention will be assessed by the validated Diet Satisfaction Score tool^(38)^ and acceptability questions related to each aspect of the intervention based on a theoretical framework of healthcare intervention acceptability^(39)^.

#### Medical outcomes

We will access participant medical records to extract breast cancer diagnostic and treatment information and for chemotherapy outcomes (relative dose intensity, chemotherapy dose reductions and delays). We will also assess incident diagnoses of cardiometabolic conditions (hypertension, dyslipidemia, type 2 diabetes, CVD and non-alcoholic fatty liver disease) at the 2-year follow-up.

#### Safety outcomes

We will provide all participants with a Fibit body weight smartscale at baseline to take home to measure their weight first thing in the morning at least every 3 weeks. Based on global malnutrition guidelines^(29)^, if participants experience weight loss of 2 % or greater since their last weigh in, a registered dietitian will follow up with the participants to screen for the possible cause of weight loss and provide nutrition education and goals to minimise further weight loss. A 1-week follow-up will be scheduled to evaluate further weight changes. The participant’s treating oncologist will be notified if the participant continues to lose weight at the 1-week follow-up, or if weight loss at any 3-week weight check-ins exceeds 5%. Selected CTC-AE relevant to nutritional impact will be evaluated during the intervention at each of the support phone calls and through patient medical records collected via standard of care. At the support calls, participants will be asked if they have experienced each adverse event. If they respond positively, they will be further probed to ascertain the severity/grade and origin of the adverse event, and if relevant, the duration. Due to very low risk of major adverse events from our intervention, study investigators will assess safety outcomes on a case-by-case basis in lieu of a data safety monitoring committee.

### Sample size

The proposed sample size of *n=*130 was calculated using the primary outcome of visceral AT at the end of chemotherapy on GLIMMPSE software (https://glimmpse.samplesizeshop.org/). To calculate sample size, we used the average visceral AT change and its correlation between time points generated by our TRE pilot study (–4·8%) using identical MRI methods. For the comparison group, we used an average change of +6·6 % which we previously observed during 12 weeks of chemotherapy in a similar patient group at one of the included institutions^(40)^. For the time correlation matrix, we used the correlations between time points observed in our pilot data (*r* = 0·9866). However, to allow for an expected increase in variability induced by chemotherapy, we estimated a 25 % increase in variability (1·25 scale factor for covariance matrix) and standard deviation at the end of chemotherapy. Using the above values, *n=*116 total participants would provide 90 % power to detect a group × time interaction with *P* ≤ 0·05 for the Hotelling–Lawley trace test (which most closely approximates mixed models). We estimate a 12 % total loss to follow-up based on rates reported for TRE studies (∼10 %)^(41)^ plus 2 % for technical difficulties. Therefore, we will recruit *n*=130 total participants (*n*=65 per group).

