Diet and physical activity interventions play important roles in the treatment of metabolic abnormalities and body composition. Intermittent fasting is a pattern of eating involving voluntary abstinence from food alternated with periods of *ad libitum* eating (unrestricted amount and content). A variety of intermittent fasting formats have been examined during chemotherapy for breast cancer and have shown promise as safe interventions with positive effects on quality of life and treatment toxicity in women undergoing chemotherapy for breast cancer^(17)^. Time-restricted eating (TRE) is a form of intermittent fasting that involves *ad libitum* energy intake within a set window of time, commonly 8 h, followed by 16 h of fasting (16:8 TRE) daily. To our knowledge, TRE has not been studied during chemotherapy but shows promise as a feasible and effective therapy to mitigate metabolic toxicity from chemotherapy.

TRE has positive cardiometabolic health effects, including reduced body fat (whole body, visceral, liver and intermuscular^(18–22)^, inflammatory markers (IL-6 and TNF-*α*), adipokines (leptin and adiponectin), and improved lipid profile, fasting glucose, insulin sensitivity, and blood pressure^(18,19,23)^. TRE is also feasible, with adherence typically > 85 % among adults with obesity, metabolic syndrome or diabetes^(18)^. We recently demonstrated feasibility, safety and participant acceptability of 8 weeks of TRE in breast cancer survivors 3 years post-chemotherapy^(24)^. Our intervention also resulted in a 5 % reduction in visceral fat, a 1·0 kg decrease in whole-body fat mass, and a 15 % relative reduction in the Framingham 10-year CVD risk score^(24)^.

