Appropriate nutrition and healthy eating practices can also reduce the burden of chemotherapy symptoms and improve health across the cancer continuum. Dietary intake and physical activity are inextricably linked to cardiometabolic disease risk through reciprocal contributions to energy balance and obesity. Outside of sleep, time spent not being physically active is considered sedentary time, defined as any waking behaviour done while sitting, reclining or lying down that expend ≤ 1·5 metabolic equivalents. Sedentary time has consistently shown to be higher in cancer survivors than controls^(25,26)^. Recently, we found that within the year after starting chemotherapy for breast cancer, whole-body and visceral fat accumulation were associated more strongly with an objectively measured increase in sedentary time (*r* = 0·47 & 0·51, respectively, both *P* < 0·001, unpublished) than either moderate-intensity physical activity or cardiorespiratory fitness, which are the focus of current exercise guidelines for cancer patients. These findings demonstrate a need for alternative approaches to energy balance during chemotherapy for early-stage breast cancer to attenuate fat accumulation.

The purpose of the Impact of Metabolic health Patterns And breast Cancer over Time in Women (IMPACT-Women) trial is to evaluate the effect of a multimodal behavioural intervention involving TRE, healthy eating and reduced sedentary time on ectopic AT and cardiometabolic profile *versus* usual cancer care in women receiving chemotherapy treatment for early-stage (I–III) breast cancer. We hypothesise that the intervention will attenuate ectopic AT, markers of metabolic dysfunction and CVD risk, and chemotherapy symptoms. Our secondary hypothesis is that the intervention effects on the cardiometabolic profile and incident diagnoses will persist to a 2-year follow-up.

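### The 90% power assumes that women on chemotherapy will lose visceral fat as women off chemotherapy did; at the same n, power is about 47% for a 6.6-point difference and 28% for 4.8 points

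*Protocol article*

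**What the plan says.** The Sample size section of the protocol article takes its two means from two different settings.

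- **Intervention arm:** the change is "generated by our TRE pilot study (–4·8%) using identical MRI methods". The introductory text before Methods describes that pilot as "8 weeks of TRE in breast cancer survivors 3 years post-chemotherapy".
- **Comparison arm:** "For the comparison group, we used an average change of +6·6 % which we previously observed during 12 weeks of chemotherapy".
- **Correlation between time points:** "we used the correlations between time points observed in our pilot data", with r = 0.9866.
- **Allowance for chemotherapy:** "we estimated a 25 % increase in variability (1·25 scale factor for covariance matrix) and standard deviation at the end of chemotherapy". No corresponding adjustment is made to the intervention-arm mean.

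From these inputs the section derives 116 evaluable women for 90% power on the group × time interaction at the 0.05 level, and 130 recruited. The hypothesis reads: "We hypothesise that the intervention will attenuate ectopic AT, markers of metabolic dysfunction and CVD risk, and chemotherapy symptoms". The Abstract and the last paragraph of the Discussion express the hoped-for result as a weakening of chemotherapy's effect on visceral fat accumulation.

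**The concern.** Everyone in this trial receives chemotherapy. The comparison-arm figure contains the chemotherapy gain. The intervention-arm figure is a before-after change in women who were not on chemotherapy, so it does not. The difference between them, 6.6 − (−4.8) = 11.4 points, is reached only if the intervention both cancels the gain seen in the earlier chemotherapy cohort and produces the full pilot loss as well.

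The authors saw that chemotherapy would alter the pilot inputs, because they inflated the variability for that reason. They left the mean alone and gave no argument for doing so. A reader who sees 90% power will assume that it covers the effect described in the Abstract and Discussion, which is less accumulation than under usual care. For an intervention that prevents a 6.6-point gain without net loss, the chance of a significant result is close to even.

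**Working it through.** **Inputs from the Sample size section:** changes of −4.8% and +6.6%; 116 evaluable (58 per arm, 1:1); 90% power; alpha 0.05; r = 0.9866; SD ratio k = 1.25 (end of chemotherapy to baseline). The base SD is not given, so n = 116 cannot be reproduced independently. I take the stated 90% as correct and back-solve the SD.

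**Step 1: implied SD of change.** With two time points the interaction test is a two-sample t test on change, with 114 df and noncentrality (δ/SD)·√(58/2).
- 90% power needs δ/SD = 0.607.
- SD of change = 11.4/0.607 = 18.8 points. The plan's 90% is then reproduced by construction.
- Var(change)/Var(baseline) = 1 + k² − 2rk = 1 + 1.5625 − 2.4665 = 0.0960.
- Baseline SD = 18.8/√0.0960 ≈ 60.6% of the baseline mean. If the covariance matrix is scaled by a further 1.25, this is about 55%. The power figures below do not change.

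**Step 2: power at other true differences, same SD.**

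| True difference | Meaning | 116 evaluable | 130 evaluable |
|---|---|---|---|
| 11.4 | intervention −4.8%, control +6.6% | 90% | 93% |
| 9.0 | | 73% | 77% |
| 8.0 | | 62% | 67% |
| 6.6 | intervention 0%, control +6.6% | 47% | 51% |
| 4.8 | intervention +1.8%, control +6.6% | 28% | 30% |

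The 4.8-point row lets the pilot change act on top of the chemotherapy gain: 6.6 − 4.8 = +1.8. Only the ratio to 11.4 enters, so the missing base SD does not affect these figures. If the test has 2 df over three time points, with the effect scaled in proportion, the 6.6-point figure is 44% instead of 47%.

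**Step 3: baseline-adjusted comparison under the plan's own covariance.**
- Residual SD = 60.6 × k × √(1 − r²) = 60.6 × 1.25 × √(1 − 0.9734) = 12.4 points.
- 6.6/12.4 = 0.53, which gives 81% power; 4.8/12.4 = 0.39, which gives 55%.

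**Step 4: dependence on r (assumed value, baseline SD held at 60.6).** At r = 0.97:
- Unadjusted: SD of change = 60.6 × √0.1375 = 22.5, power for 6.6 points 35%.
- Adjusted: residual SD = 60.6 × 1.25 × √(1 − 0.9409) = 18.4, power for 6.6 points 48%.

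The gain also depends on k. With equal SDs the variance ratios are 2(1 − r) = 0.0268 unadjusted and 1 − r² = 0.0266 adjusted, so adjustment would add almost nothing.

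**The case against.** The best defence is that 6.6 points is not shown to be the upper limit. A reader might infer that attenuation can yield at most zero gain and therefore at most 6.6 points. The article does not support this. The +6.6% was observed over 12 weeks. The Outcomes section puts chemotherapy at typically 12–18 weeks, with the scan 2–6 weeks after the last treatment. If the gain were linear in time (an assumption), 18 weeks would give 6.6 × 18/12 = 9.9 points and about 80% power. The intervention also runs longer than the 8-week pilot and adds dietitian counselling and sedentary-time reduction to TRE. The hypothesis sentence does not exclude net loss. This part of the defence stands: the true contrast could exceed 6.6 points. The article, however, gives no figure for it and does not use the argument to justify −4.8%.

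A reader might also infer that 6.6/11.4 = 58% of the planned contrast is a difference between settings and no treatment effect. That does not follow, because preventing a 6.6-point gain would itself be a treatment effect. The comparison-arm mean suits this trial; the intervention-arm mean is the open question.

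A third tempting reading is that the variance allowance is inadequate because the pilot correlation was kept. On the model above, the 1.25 SD ratio already raises the variance of change from 0.0268 to 0.0960 in units of the baseline variance, 3.6-fold. Nothing in the article supports a lower r on top of that. A lower r belongs only in a labelled sensitivity analysis.

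Finally, the inputs and their sources are openly stated, and the fix leaves the sample size and endpoint alone. That argues against treating the point as a fatal flaw.

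**Conclusion.** The point holds as a should-fix. The 90% power is conditional on the intervention arm losing 4.8% of visceral fat during chemotherapy while controls gain 6.6%. The loss is borrowed from women off chemotherapy and is not adjusted or justified for this setting. At the same evaluable n, power is about 47% for a 6.6-point difference (44–51% depending on test df and retention) and about 28% for 4.8 points.

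These figures assume that the stated 90% at 116 is correct, that baseline means are equal, and that the back-solved SD of change of about 18.8 points applies at every true difference. They do not show that 130 is the wrong sample size or that the assumed effect is impossible. They show that the quoted power does not carry over to smaller effects that fit the stated aim.

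**What to change.** 1. Keep n = 130. In the Sample size section, state that 90% power holds only if the intervention arm loses 4.8% while controls gain 6.6%, and that the loss comes from women 3 years after chemotherapy.
2. Give power at 6.6 points (about 47%; 51% if all 130 are evaluable) and at 4.8 points (about 28%) as sensitivity values. If the authors expect a larger contrast because of longer follow-up or the added components, they should give the figure and its basis.
3. In the Analyses section, make the primary comparison at the end of chemotherapy baseline-adjusted, either with baseline visceral fat as a covariate or with a mixed model that constrains the baseline means to be equal. Under the plan's own covariance this gives about 81% and 55% at the same n. State that this gain depends on r (about 48% at 6.6 points for an assumed r of 0.97) and on the 1.25 SD ratio.
4. Show any lower r only as a labelled sensitivity value.

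The cost is a change of wording and of the primary model specification, made before any outcome is compared by arm. The baseline scan is already collected, so no extra patients or visits are needed. The stated power becomes less favourable.

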## Methods

### Study design, randomisation and blinding

IMPACT-Women is a two-site, two-arm, parallel-group superiority randomised controlled trial. Participants will be randomised 1:1 to the two groups using permutated blocks with random block sizes of two and four, stratified by study site, chemotherapy type (adjuvant/neoadjuvant), and postmenopausal status (yes/no). Randomisation will occur after completion of baseline assessments using a blinded online electronic randomisation tool, with enrolment and assignment performed by a research coordinator. All outcome assessors will be blinded to group assignment. Blinding participants to a behavioural intervention is not possible but is not expected to bias our physiological outcomes. Participants’ treating oncologists will not be blinded as we expect that group assignment may need to be discussed during care.

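### Minor: recruiting 130 does not follow from 116 evaluable and 12% loss; 130 leaves about 114, with power of about 89.5% to just under 90%

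*Protocol article*

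**What the plan says.** All the figures are in the Sample size section of the protocol article.

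- **Evaluable number and power.** The section gives 116 and says that this many "total participants would provide 90 % power to detect a group × time interaction", with the threshold set at "0·05 for the Hotelling–Lawley trace test (which most closely approximates mixed models").
- **Loss.** "We estimate a 12 % total loss to follow-up based on rates reported for TRE studies". The 12% is made up of roughly 10% from other studies of time-restricted eating, "plus 2 % for technical difficulties".
- **Recruitment.** The next sentence presents the target as a consequence of these figures: 130 "total participants (*n*=65 per group").
- **Allocation.** The Study design section says "Participants will be randomised 1:1 to the two groups".

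The article does not print the formula that leads from 116 to 130. Nor does it say in so many words that 116 will remain after the loss.

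**The concern.** The only reason to add participants for expected loss is that the number needed for the stated power should still be there at the end. The recruitment target is introduced as following from the 116 and the 12%, so a reader will take it that 130 recruited, less 12%, leaves 116. It does not: it leaves about 114.

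The usual cause is applying the loss rate to the wrong base. A loss to follow-up is a fraction of those recruited, so the evaluable number must be divided by one minus the rate. Multiplying by one plus the rate always falls short, and here it gives exactly the printed figure.

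At stake is whether the size, loss rate and power given for the primary outcome agree. The error is in the optimistic direction, and any reader who checks the section will find it.

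**Working it through.** **Inputs, all from the Sample size section:** evaluable total 116; power 90%; alpha 0.05; total loss 12% (about 10% plus 2%); recruited total 130, in two equal groups.

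**1. Reproducing the plan's figure.**
116 × (1 + 0.12) = 129.92, which rounds to 130. The match is exact, so this is very probably the step taken, but it is an inference.

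**2. The number that 12% loss requires.**
116 / (1 − 0.12) = 116 / 0.88 = 131.8. Rounded up, this is 132, or 66 per group.
Check: 132 × 0.88 = 116.2, which covers 116.
Taking the two losses in sequence gives the same answer: 116 / 0.90 / 0.98 = 131.5, so again 132.

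**3. What 130 delivers.**
130 × 0.88 = 114.4, so about 114 evaluable (57 per group), about 2 short of 116.
Largest loss that still leaves 116: 1 − 116/130 = 0.108, or 10.8%.

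**4. Power at 114.** The plan takes the mean changes as "generated by our TRE pilot study (–4·8%) using identical MRI methods" for the intervention and "For the comparison group, we used an average change of +6·6"% for the comparison group. The visceral fat mean and standard deviation are not printed, so the 116 cannot be rebuilt from these. The power can only be scaled from the plan's own claim. With two groups and two time points, the group-by-time test is an F test with 1 and N − 2 degrees of freedom and noncentrality d²N/4, where d is the standardised difference in change.

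| Assumption about 116 | Implied d | Power at 116 | Power at 114 |
|---|---|---|---|
| 116 gives exactly 90.0% | 0.607 | 90.0% | 89.5% |
| 116 is the smallest even total reaching 90%, so 114 falls just short (limiting case) | just under 0.612 | just under 90.5% | just under 90% |

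A normal approximation in the first case also gives 89.5% at 114. At the unrounded 114.4, power is 89.6%.

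**The case against.** The case against giving this any weight is strong on size.

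- **The gap is tiny.** It is 2 participants in 132 (1.5%), one per group, and at most about half a percentage point of power. In terms of variability, 116 against 114 corresponds to an error of under 1% in the standard deviation (√(116/114) = 1.009). The plan's 25% increase in variability for chemotherapy is itself an estimate, and its intervention effect comes from a pilot in women 3 years past chemotherapy. Those uncertainties are far larger. This stands, and it is why the point is minor.
- **The 12% is approximate.** It rests on a rate that the article itself marks as approximate, and 130 would suffice if the loss were 10.8%. This stands as context. But 12% is the rate the plan chose and built its target on, and imprecision in a rate does not change how it should be applied.
- **The analysis is not restricted to completers.** The Analyses section plans an intention-to-treat mixed model, and the Outcomes section asks participants who stop or deviate from the intervention to complete all assessments. This may soften the effect. However, a woman without the post-chemotherapy MRI contributes no value for the primary outcome, and the Sample size section itself treats the 12% as loss to be made up by extra recruitment.
- **The formula is not stated.** That is correct, so multiplication by 1.12 should be reported as the likely explanation and not as fact. The discrepancy does not depend on it.

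A reader might go further and infer that the trial is underpowered, or that power drops to about 89%. The document does not support either. The figure of 89.5% is the low end of the range. It applies if 116 gave exactly 90.0%; if 116 was the smallest even total to reach the target, power at 114 could be just under 90%.

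**Conclusion.** The point holds as a minor error in the text. The recruitment figure of 130 does not follow from 116 evaluable and 12% loss; the figure that does is 132. Both the direct and the sequential calculation agree on this, and neither needs any input beyond those printed in the Sample size section. A fuller protocol or analysis plan could not make the three printed numbers agree.

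The consequence is small: about 114 evaluable in place of 116, and power of about 89.5% to just under 90% in place of 90%. This range assumes that the plan's claim of 90% at 116 is right, that losses are equal in the two groups, and that those lost contribute nothing to the primary comparison. It does not show a design defect, and it gives no reason to change enrolment.

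**What to change.** Keep 130 and correct the sentence in the Sample size section in one of two ways:

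- state that 130 recruited with 12% loss leaves about 114 evaluable participants (57 per group), with about 89.5% power under the same assumptions; or
- state that 130 preserves 116 evaluable participants, and so the 90% power, for a total loss of up to 10.8%.

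The cost is one sentence. If the 12% loss is kept, the stated power is lower by at most about half a percentage point; if the 90% power is kept, the loss allowance drops from 12% to 10.8%. Recruitment, randomisation and analysis are unaffected.
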